**Table 1 Tab1:**
[figure not shown]
Sequential Organ Failure Assessment (SOFA) score. *PaO*_*2*_ partial pressure of oxygen, *FiO*_*2*_ Fraction of inspired oxygen

### Secondary outcomes

The main secondary endpoints include: mean SOFA score from day 0 to day 4 after exclusion of the neurological subscore; daily SOFA scores from day 0 to day 4; daily SOFA subscores for each organ/system from day 0 to day 4; variation of SOFA scores from day 0 to day 4; number of days alive without organ support (i.e., invasive mechanical ventilation, renal replacement therapy, or vasoactive drugs) on day 28; length of ICU and hospital stay; all-cause mortality in ICU, hospital, on day 28 and on day 90.

### Data collection

The following data are recorded: demographics, concurrent medical conditions and comorbidities, sepsis diagnosis and treatment, severity of illness and organ dysfunction scores, vital signs and laboratory results, characteristics of the RECO procedure, life-sustaining therapies, and outcomes (follow-up: 90 days). Data are entered into a web-based electronic case report form (eCRF, ClinSight™ software) from patient notes (source) under the supervision of the trial site investigators. A unique numeric identifier is assigned to each patient. All the data entered in the study database are anonymized in order to ensure confidentiality. Assessments are made at inclusion, and on days 1, 2, 3, 4, 28, and 90. From the eCRFs, the trial database will be established. According to French laws, all original records (including informed consent forms, eCRF, and relevant correspondences) will be archived at trial sites for 25 years.

### Safety

Given that the trial is being conducted in critically ill patients, a significant number of patients are likely to experience adverse events (AEs) not related to the intervention. Therefore, only grade-3 or more AEs are reported. The following clinical outcomes from sepsis will not be recorded as AEs unless the local investigator deems the event to be related to the study: cardiovascular failure, respiratory failure, hepatic failure, renal failure, hematological failure, or neurological failure. While no significant RECO-related AE is expected based on previously published studies, all mechanical complications related to the use of the blood pressure cuff and leading to a medical/surgical intervention are systematically reported as serious AEs to the sponsor center within 24 h and to the relevant authorities in accordance with current French regulations. Any death occurring within 90 days after inclusion is also reported as a serious AE. All AEs are assessed for relationship with the tested intervention. No data safety monitoring board will be ask to monitor the study.

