To the best of our knowledge, RECO has not been tested in patients with septic shock. We have, therefore, implemented a multicenter, randomized controlled trial (RECO-Sepsis study) to investigate whether ischemic conditioning applied by inflating/deflating a cuff around an upper limb would limit the severity of MOF in septic shock patients.

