### Intervention

As soon as possible after randomization to either the RECO group or the Control group, a standard CE-approved blood pressure cuff (Tensiomètre Manopoire Duo Colson®, Drive DeVilbiss Healthcare, Frouard, France) is placed, deflated, around one of the patient’s upper arms. In line with the recommendations for non-invasive measurement of blood pressure, the size of the cuff is chosen to accommodate the patient’s arm [23]. In the RECO group, ischemic conditioning consists of four cycles of cuff inflation to 200 mmHg for 5 min and then deflation to 0 mmHg for another 5 min (40 min total duration of the intervention). Both the safety and the efficacy of this standard protocol has been demonstrated in previous clinical trials [5–7, 9–13]. In the Control group, the cuff is left in place, deflated, for 40 min (sham procedure). The RECO or the sham procedure is repeated at 12 and 24 h after inclusion. Standard operation procedures (SOP) describing the interventions are available for all investigators. A written checklist is completed by the investigator performing the intervention to ensure protocol adherence. With the exception of the tested intervention, patients receive standard care in accordance with international guidelines [2].

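### The described adverse-event reporting leaves out grade 1–2 cuff-site events that need no intervention, so mild or moderate local tolerability of the 12 planned inflations is not covered

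*Protocol article*

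**What the plan says.** Three parts of the protocol article bear on this.

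- **Safety.** The section opens by expecting that "a significant number of patients are likely to experience adverse events (AEs) not related to the intervention", and draws the consequence directly: "Therefore, only grade-3 or more AEs are reported". Sepsis-related organ failures are exempted from adverse-event recording unless the local investigator considers them related to the study. For the cuff there is one specific rule: "all mechanical complications related to the use of the blood pressure cuff and leading to a medical/surgical intervention are systematically reported as serious AEs". These go to the sponsor within 24 h. The rule is prefaced by a concession about earlier evidence: "While no significant RECO-related AE is expected based on previously published studies". On causality, the section says "All AEs are assessed for relationship with the tested intervention".
- **Intervention.** A RECO session is four 5-minute inflations to 200 mmHg. Sessions take place at inclusion and at 12 and 24 h. Controls wear a deflated cuff for the same 40 minutes. "A written checklist is completed by the investigator performing the intervention to ensure protocol adherence".
- **Background.** The authors state that, to their knowledge, "RECO has not been tested in patients with septic shock".

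The Data collection section lists procedure characteristics among the recorded data without saying what they comprise.

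**The concern.** The grade-3 threshold has a sensible purpose: it keeps the background events of septic shock from swamping the safety data. Local effects under the cuff, such as bruising, skin marks, pain or transient perfusion changes, are a different kind of event. Their site and timing point to the procedure, so the background argument does not explain leaving them out. As written, the threshold treats them like any other low-grade event.

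The organ failures that are exempted from adverse-event recording are still measured through SOFA, organ support and mortality. Mild local effects have no such second route.

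At stake is a modest but useful piece of information. The Discussion presents the trial as a source of data for designing later trials with a hard endpoint, and how well repeated inflation is tolerated in patients on norepinephrine is part of that. If the report says that no cuff complications occurred, readers need to know which grades the statement covers.

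**Working it through.** **1. Which cuff-site events are reported under the stated rules**

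| Cuff-site event | Reported? | Rule |
|---|---|---|
| Needs a medical or surgical intervention | Yes, as a serious event | Cuff provision |
| Grade 3 or higher, no intervention | Yes | General threshold |
| Grade 1–2, no intervention | No | Neither rule applies |

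The cuff provision adds a route and excludes nothing. The gap in the last row comes from the grade-3 threshold alone. The relatedness assessment does not close it, because it applies to events that have already qualified for reporting.

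**2. Whether another described measure fills the gap**

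The primary outcome is mean daily SOFA. The listed secondary outcomes are SOFA variants, days alive without organ support, length of stay and mortality. None measures a local limb effect. The checklist's stated purpose is adherence.

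**3. Exposure**

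- Per RECO patient: 3 sessions × 4 cycles = 12 inflations; 12 × 5 min = 60 min of inflation over about 24 h.
- In the RECO arm: 90 × 12 = 1,080 planned inflations.

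**4. The plan's own figure**

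The article gives no safety or tolerability figure. The denominator of 90 comes from the Sample size section, which reproduces closely. An effect size of 0.5, 90% power and two-sided 5% alpha give 85 per arm (170 in total) against the stated 168. Power at 84 per arm is 89.98% by the normal approximation and 89.6% by the t-test. The allowance is 168 + 12 = 180, or 90 per arm.

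**5. What zero reported events would mean**

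With 0 events in n patients, the 95% upper limit is 1 − 0.05^(1/n) one-sided and 1 − 0.025^(1/n) two-sided exact.

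- n = 90: 1 − 0.05^(1/90) = 3.3%; 1 − 0.025^(1/90) = 4.0%.
- n = 84 (168 ÷ 2, without the allowance): 3.5% and 4.3%.

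Under the stated rules these limits apply only to the first two rows of the table.

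**6. Illustration for milder events (assumed rates)**

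The article gives no rate for mild local effects. If 5%, 10% or 20% of RECO patients had one, the expected numbers outside adverse-event reporting would be 90 × 0.05 = 4.5, 90 × 0.10 = 9 and 90 × 0.20 = 18. This shows scale only and is not evidence of a loss.

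**The case against.** The case for leaving the plan alone is reasonable. A selective threshold is a considered choice in this population. Local tolerability is not a stated objective. The harms that matter most are reported, with those leading to intervention on a 24 h route. The article is condensed: the case report form, the checklist and the operating procedures are not shown and may already note early stops or local effects. A count of mild events would also be imperfect, because the trial is open-label, the person performing the procedure would score them, and most patients are expected to lack capacity to consent, so pain would be poorly ascertained.

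Most of this stands, and it rules out several stronger readings:

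- A reader might infer that the trial cannot report or compare local harm at all. It can for grade 3+ and intervention-requiring events, since both arms wear a cuff.
- A reader might infer that milder events go unrecorded everywhere. The Safety text limits what is reported as adverse events; what the procedure forms hold cannot be judged.
- A reader might infer that the threshold rests on safety evidence from other populations. The article ties it to unrelated background events. The clause on earlier studies introduces the additional cuff provision.

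What the objection does not answer is the mismatch between the threshold's stated reason and the events under the cuff. The rule is explicit and carries no exception for the cuff site, so this is more than detail left to a fuller document.

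**Conclusion.** The point holds in a limited form and is minor. The described adverse-event reporting omits grade 1–2 cuff-site events needing no intervention. The reason given for the threshold does not extend to them, and no listed outcome captures them. Mild or moderate local tolerability of the 12 planned inflations is therefore not covered by the safety reporting as described, in what the authors believe is the first trial of RECO in septic shock.

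The consequence is one of interpretation. Zero reported events in 90 RECO patients would bound the more severe events at 3.3% (one-sided; 4.0% two-sided exact), assuming that all 90 are treated and assessed, and would say nothing about milder ones. How many milder events might be missed is unknown; any rate is an assumption. The conclusion would weaken further if the unseen forms already collect these items. Detection of serious cuff harm, the primary endpoint and the sample size are unaffected.

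**What to change.** Exempt cuff-site events from the grade-3 threshold. First check whether the case report form or checklist already holds the items below. If not, add to the per-session checklist, in both arms:

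- any cuff-site event, of any grade;
- whether the session was stopped early, and why.

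Report counts by arm as descriptive safety data. State that open-label assessment and patients' limited ability to report pain may bias the comparison. Leave the grade-3 threshold for all other adverse events and the 24 h serious-event route as they are.

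The cost is a few tick-boxes at up to three sessions per patient and one extra table, with no added procedure. Recruitment was under way when the article was written, so for patients already treated the items may be unavailable; the report should say from when they were collected.

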### Monitoring

Monitoring on site of all centers is performed by the study sponsor. The monitor will review the entries into the eCRF on the basis of source documents. Monitors will review the consent forms and all data contributing to the primary outcome. The investigators must give access to all essential source data and must provide support at all times to the monitor. The monitor also ensures regularly that the trial is conducted according to the protocol and regulatory requirements. In each center, a monitoring is planned after the enrollment of the first two patients and afterwards after every six patients.

### Study organization

The RECO-Sepsis study is coordinated by the Clinical Investigation Center (CIC) located in Lyon, France. Each participating center has a senior investigator as principal investigator with strong clinical trial experience. All trial-related processes follow the SOP of the RECO-Sepsis study protocol. The RECO-Sepsis Steering Committee is co-chaired by [name], PhD and [name], PhD (Claude Bernard University of Lyon 1 – Edouard Herriot Hospital, Lyon, France). The Steering Committee is responsible for the scientific content of the protocol and oversees the trial operations. The Steering Committee will have full access to all the data in the study and will have final responsibility for the decision to submit the results for publication.

### Sample size

No a priori evidence suggests the magnitude of the effect of RECO on the severity of MOF in septic shock patients. Under the alternative hypothesis of an expected difference of half the standard deviation (effect size: 0.5) of the mean daily SOFA score of the first 4 days after inclusion, at least 168 patients have to be enrolled to reject the null hypothesis of a similar mean SOFA score in both arms with a power of 90% (β = 10%) and type 1 error at α = 5% (two-tailed). Even though there is no published data regarding the mean daily SOFA score in patients meeting our eligibility criteria, one can assume a mean value ranging from 8 to 12 with a standard deviation ranging from 4 to 6. Thus, for example, if the standard deviation is found to be 4, then a decrease of 2 or more in the mean daily SOFA score will be needed to reach significance. We planned to recruit an additional 7% patients (*n* = 12) to account for potential loss to follow-up and withdrawal of consent. Thus, the planned sample size is 180 patients (90 patients in each arm). Based on the enrollment capacity of the participating centers, the recruitment is expected to be completed within 18 months. The sample size was calculated with the use of nQuery Advisor, version 5.0 (Statistical solution, Cork, Ireland).

### Statistical analysis

The trial will end once 180 patients have been enrolled and have completed the 90 days’ follow-up. No interim analysis will be planned for this study. A full statistical analysis plan will be drawn up by the CIC (Lyon) before the trial database is locked. Prior to performing any statistical tests or fitting statistical models, an exploratory analysis of the baseline variables will be completed. The number and pattern of missing data for baseline variables and outcomes will be established by forming appropriate tables and likely causes of any missing values will be investigated. Variables will be expressed as median and interquartile range (IQR) or number and proportion, as appropriate. Statistical analyses of the primary and secondary efficacy endpoints will primarily be based on the intent-to-treat population. The main analysis of the primary endpoint, the mean daily SOFA score from day 0 to day 4, will be performed by fitting a mixed-effects linear model with a fixed effect for the assigned treatment and a random centre effect. Secondary outcomes will be analyzed with appropriate statistical methods including the Wilcoxon rank sum, chi^2^ and log-rank tests. The same analysis will be performed on the per-protocol population, which will include all randomized patients who have received the intervention in accordance with the allocated group without any major protocol deviation. A probability value of < 0.05 will be considered to indicate statistical significance and 95% confidence intervals will be calculated.

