**Methods/design:**

RECO in septic shock patients (RECO-Sepsis study) is an ongoing, prospective, multicenter, randomized, open-label trial, testing whether RECO, as an adjuvant therapy to conventional treatment in septic shock, decreases the severity of MOF as assessed by the Sequential Organ Failure Assessment (SOFA) score. Adult patients admitted to an intensive care unit with documented or suspected infection, lactatemia > 2 mmol/l, and treated with norepinephrine for less than 12 h are potentially eligible for the study. Non-inclusion criteria are: having expressed the wish not to be resuscitated, contraindication for the use of a brachial cuff on both arms, intercurrent disease with an expected life expectancy of less than 24 h, cardiac arrest, and pregnant or breastfeeding women. After enrollment, patients are randomized (*n* = 180) 1:1 to receive RECO or no adjunctive intervention. RECO consists of four cycles of cuff inflation to 200 mmHg for 5 min and then deflation to 0 mmHg for another 5 min. RECO is performed at inclusion and repeated 12 and 24 h later. The primary endpoint is the mean daily SOFA score up to day 4 after inclusion. Secondary outcomes include the need for organ support, hospital length of stay, and 90-day mortality.

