### Primary outcome

The primary outcome of this trial is the severity of sepsis-induced MOF as assessed by the mean daily SOFA score from inclusion (day 0) to the fourth day after inclusion (day 4) or to the day of death if it occurs before day 4. The SOFA score is an objective tool to quantitatively describe the degree of organ dysfunction over time [18–21]. The mean daily SOFA score, which closely correlates with mortality in critically ill patients [19], is regularly used as a surrogate outcome for death in sepsis trials [24, 25]. The choice of a mean SOFA score helps to solve the “truncated by death” issue as all patients contribute scores and no imputation of data is needed if a patient dies. As shown in Table 1, the SOFA score ranges from 0 to 24 (higher scores indicate more severe organ failure), with 0 to 4 points assigned for each of six organ dysfunctions (i.e., respiratory, coagulation, liver, cardiovascular, central nervous system, and renal). As previously described, a daily SOFA score is calculated using the most abnormal clinical and/or biological values in the previous 24 h (or from the start of the considered 24-h period to death) [18–21]. Predefined rules for dealing with potential missing data have been established.

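### The primary model adjusts for centre only; prespecifying day-0 SOFA as a covariate would gain precision at almost no cost, provided the day-0 score closes before the first procedure

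*Protocol article*

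**What the plan says.** The Statistical analysis section gives the main analysis of the primary endpoint as "fitting a mixed-effects linear model with a fixed effect for the assigned treatment and a random centre effect". It names no baseline covariate and mentions no adjusted analysis of the primary endpoint. A full statistical analysis plan is promised before database lock; it is not shown.

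The Primary outcome section defines the endpoint as "the mean daily SOFA score from inclusion (day 0) to the fourth day after inclusion (day 4) or to the day of death", if death comes before day 4. Day 0 is therefore one of the averaged scores. On timing, the same section says that "a daily SOFA score is calculated using the most abnormal clinical and/or biological values in the previous 24 h", and the Data collection section says "Assessments are made at inclusion, and on days 1, 2, 3, 4, 28, and 90". The abstract says "RECO is performed at inclusion and repeated 12 and 24 h later".

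The Randomization section stratifies by centre only. The Sample size section uses no covariate: it assumes "an expected difference of half the standard deviation (effect size: 0.5)", "with a power of 90% (β = 10%) and type 1 error at α = 5% (two-tailed)", which gives 168 evaluable patients, raised to 180. On the outcome scale, "one can assume a mean value ranging from 8 to 12 with a standard deviation ranging from 4 to 6".

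**The concern.** A baseline measurement of the outcome normally predicts the later outcome. Here the link is partly built in: day 0 is one fifth of the mean in a patient with all five scores, and one half in a patient who dies on day 1. Nothing in the design balances baseline organ failure between arms, because stratification is by centre alone. A model with only treatment and centre therefore carries variance that a covariate already in the database could remove, and part of any chance day-0 difference between arms stays in the treatment estimate.

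At stake is the width of the confidence interval and the smallest effect that the trial can detect. This matters for a proof-of-concept trial that is meant to inform the design of later trials.

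Timing matters too. The trial is open-label, and baseline variables are to be explored before any model is fitted. A covariate added late to a model that the protocol has already stated could look data-driven.

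**Working it through.** **Inputs from the article.** Effect 0.5 SD, two-sided 5% test, power 90%, 84 evaluable patients per arm (168 in total), 90 randomised per arm, outcome SD 4 to 6.

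**Assumed input.** ρ, the within-arm correlation between day-0 SOFA and the day 0-4 mean, is not in the article. It is varied from 0.3 to 0.8. The centre effect is left out here; the Sample size section mentions none either.

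**Step 1: reproduce the plan's figure.** n per arm = 2(1.960 + 1.282)² / 0.5² = 84.06. The plan's 84 per arm has power 90.0% by the normal approximation (89.6% by the noncentral t). Inflation: 168 × 1.07 = 179.8, hence 180. The stated sample size reproduces without adjustment.

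**Step 2: add day-0 SOFA.** The residual SD is SD × √(1 − ρ²), so the share of within-arm variance removed is ρ². Then:

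- n per arm = 84.06 × (1 − ρ²), rounded up
- power = Φ(0.5 / √(1 − ρ²) × √(84/2) − 1.960)
- difference detectable with 90% power = 0.50 × √(1 − ρ²) SD

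| ρ | Variance removed | n per arm for 90% power | Power at 84 per arm | Detectable difference (SD) | In points, SD 4 | In points, SD 6 |
|---|---|---|---|---|---|---|
| 0 (as planned) | 0% | 85 | 90.0% | 0.50 | 2.00 | 3.00 |
| 0.3 | 9% | 77 | 92.5% | 0.48 | 1.91 | 2.86 |
| 0.4 | 16% | 71 | 94.2% | 0.46 | 1.83 | 2.75 |
| 0.5 | 25% | 64 | 96.3% | 0.43 | 1.73 | 2.60 |
| 0.577 | 33% | 57 | 97.8% | 0.41 | 1.63 | 2.45 |
| 0.6 | 36% | 54 | 98.2% | 0.40 | 1.60 | 2.40 |
| 0.7 | 49% | 43 | 99.5% | 0.36 | 1.43 | 2.14 |
| 0.8 | 64% | 31 | over 99.9% | 0.30 | 1.20 | 1.80 |

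**Step 3: which ρ is plausible?** The part-whole overlap sets a starting point. With equal daily SDs and the same correlation r between any two days, the covariance of day 0 with the mean and the variance of the mean are both (1 + 4r)/5 in units of the daily variance. So ρ² = (1 + 4r)/5, and the variance removed under different assumptions is:

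- Equal SDs, equal correlation: 20% at r = 0, 33% at r = 0.17, 44% at r = 0.3, 60% at r = 0.5.
- Equal SDs, correlation decaying day by day (AR(1)): 25%, 34% and 50% at lag-1 correlation 0.3, 0.5 and 0.7.
- Daily SD rising from 3 to 5 (3, 4, 4.5, 5, 5), AR(1): 15%, 24% and 41% at the same lag-1 correlations.

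The gain depends on these assumptions, and the article does not decide between them.

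**Step 4: chance imbalance.** With 90 per arm, the standard error of the day-0 difference between arms is √(2/90) = 0.149 SD. An imbalance at the 95% limit is 1.96 × 0.149 = 0.292 SD. Its expected shift of the unadjusted estimate is ρ × 0.292: 0.09 SD at ρ = 0.3 and 0.23 SD at ρ = 0.8. That is about 18% to 47% of the 0.5 SD design effect.

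**Step 5: is day-0 SOFA a pre-treatment value?** Scoring over the preceding 24 hours and an assessment at inclusion suggest that it is. But the Primary outcome section also counts, for patients who die, from the start of the 24-hour period in question, and RECO begins at inclusion. If the day-0 window runs past randomisation, the covariate is partly post-treatment.

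**The case against.** Nothing in the article is contradictory here. The model is valid under randomisation, includes the stratification factor and agrees with an unadjusted sample size that reproduces. The trial meets its own power target, and adjusted analyses are often left to a statistical analysis plan. All of this stands, except that the article states the main model outright: a plan that added day-0 SOFA would be changing that model, not filling in a detail.

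A reader might infer that the omission throws away a third or more of the variance. The article does not support that figure. It needs ρ of at least 0.577 (√(1/3)), and no correlation and no day-0 SD are given. All patients enter on norepinephrine with lactate above 2 mmol/l, which may narrow the day-0 spread. For example, assume SD 3 on day 0, SD 5 for the day 1-4 mean and a correlation of 0.4 between them. The covariance with the overall mean is 0.2 × 9 + 0.8 × 0.4 × 15 = 6.6, the SD of that mean is 4.28, and ρ = 6.6 / (3 × 4.28) = 0.51, so 26% is removed.

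A reader might also infer that a chance baseline difference could not be told apart from an effect of RECO. That is too strong. The unadjusted standard error and type I error already allow for chance imbalance, and only part of the imbalance passes into the estimate.

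**Conclusion.** The point holds as one of efficiency. The stated primary model leaves out a baseline score that is already collected and forms part of the outcome. The unadjusted analysis is unbiased over randomisations and has the 90% power claimed for it.

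The size of the gain is conditional. For an assumed ρ of 0.3 to 0.8, adjustment removes 9% to 64% of the total within-arm outcome variance and lowers the detectable difference from 0.50 SD to between 0.48 and 0.30 SD. At the low end the gain is modest (power 92.5%); from ρ = 0.5 it is material (96% or more). These figures assume a linear relation and a day-0 score unaffected by treatment. The second condition has to be secured in the definition of the score before the covariate is used.

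**What to change.** - In the primary mixed model, prespecify day-0 SOFA as a continuous fixed covariate beside treatment and the random centre effect. Keep the unadjusted model as a sensitivity analysis.
- Define day-0 SOFA from values up to randomisation and before the first RECO or sham procedure.
- Extend the adjustment only to linear models of post-baseline SOFA endpoints. It cannot apply to day-0 SOFA, which the Secondary outcomes section lists among the daily scores, and it does not carry over to the rank, chi-squared and log-rank tests named for secondary outcomes.
- State how a missing day-0 component is handled, in line with the predefined missing-data rules that the Primary outcome section mentions.

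The cost is a sentence or two in the protocol or analysis plan, one more model to report, and no new data. The change should be dated before anyone sees outcome data by arm.

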### Randomization

After consent, eligible patients are randomly assigned to received RECO or not. Randomization is stratified by center on a 1:1 basis in permuted blocks. Randomization is performed online using the ClinSight™ software (Ennov Clinical Software, Paris, France).

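### The tests named for secondary outcomes take no account of centre, although randomisation is stratified by centre and the primary model includes it: mildly conservative if centre is prognostic

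*Protocol article*

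**What the plan says.** The Protocol article's Randomization section states: "Randomization is stratified by center on a 1:1 basis in permuted blocks". In the Statistical analysis section, the main analysis of the mean daily SOFA score is a linear mixed model with treatment as a fixed effect and centre as a random effect. The same section then turns to the remaining endpoints: "Secondary outcomes will be analyzed with appropriate statistical methods including the Wilcoxon rank sum", with the chi-square and log-rank tests completing the named list. It does not mention centre, stratified versions or covariates for these endpoints, and it does not say which test goes with which endpoint. It sets significance at p < 0.05, promises 95% confidence intervals without giving a method, and says that a full SAP will be written before database lock.

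The Secondary outcomes section lists SOFA-based measures, days alive without organ support, length of ICU and hospital stay, and all-cause mortality at several time points.

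**The concern.** Blocking within centre balances the arms centre by centre. Differences between ICUs therefore largely cancel from the treatment comparison. A test that ignores centre still counts those differences as noise. If centre predicts outcome, its null distribution is too wide: it rejects less often than its nominal level and gives up some power. Mortality, discharge practice and use of organ support can plausibly differ between ICUs, so the condition is not far-fetched.

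The protocol also treats centre in two ways without explanation: in the model for the primary endpoint, absent from the tests named for the rest. The Discussion expects the trial to inform later trials with a hard endpoint. Here those hard endpoints are secondary, so their precision has some value.

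**Working it through.** **Inputs from the Protocol article.** 1:1 allocation stratified by centre in permuted blocks (Randomization); two-sided 5% level, 90% power, effect size 0.5 SD, 168 patients plus 12 for losses, 180 in total or 90 per arm (Sample size). The number of centres, block size and ICC are not given. The protocol sets no effect size or power for any secondary outcome.

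**The plan's own figure.** Per arm, n = 2(1.960 + 1.282)² / 0.5² = 84.1, which rounds up to 85, or 170 in total, against "at least 168 patients have to be enrolled to reject the null hypothesis". At 84 per arm, power is 90.0% by the normal approximation. The figure reproduces. It concerns the primary endpoint only and serves here to fix the trial's size.

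**Approximation.** For a continuous mean with exact balance within centres and ICC ρ, true SE / SE used = √(1 − ρ). The size of the unadjusted test is then 2[1 − Φ(1.96/√(1 − ρ))]:

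- ρ = 0.05: 1.96/0.975 = 2.011, size 4.4%
- ρ = 0.10: 1.96/0.949 = 2.066, size 3.9%
- ρ = 0.20: 1.96/0.894 = 2.191, size 2.8%

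This shows the direction, but it does not describe the three named tests.

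**Simulation of the named tests.** Assumptions: N = 180; permuted blocks of 4 within centre; either six unequal centres (50, 40, 30, 25, 20, 15) or ten centres of 18; a normal latent severity with total variance 1 and between-centre share ρ; 3,000 runs per setting. Wilcoxon was compared with van Elteren on the latent score. Chi-square was compared with Cochran-Mantel-Haenszel on a binary event with 40% risk in the control arm. Log-rank was compared with its centre-stratified form, with worse severity giving earlier events. Power is for a latent shift of 0.5 SD. Ranges span the three tests and both centre layouts.

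| Assumed ICC | Size, unstratified | Size, stratified | Power, stratified minus unstratified (points) |
|---|---|---|---|
| 0 | 4.6-5.7% | 4.7-5.8% | -2.1 to -0.1 |
| 0.05 | 4.8-5.5% | 4.8-5.8% | -0.2 to +0.6 |
| 0.10 | 4.1-4.6% | 4.8-5.3% | -0.3 to +1.7 |
| 0.20 | 3.3-4.1% | 4.7-5.6% | +1.9 to +4.0 |

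The simulation error of a size near 5% is √(0.05 × 0.95 / 3000) = 0.4 points. At ICC 0.05 the unstratified tests are therefore nominal within error. At 0.20 they are clearly below 5%, while the stratified versions hold their level. With no centre effect, van Elteren fell from 91.1% to 90.0% (six centres) and from 91.0% to 88.9% (ten centres). Cochran-Mantel-Haenszel and the stratified log-rank test lost under 1 point.

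**The case against.** The strongest reply is that this belongs in the SAP. Whether a secondary log-rank or chi-square test is stratified is ordinary SAP content, a SAP is promised, and the article never says that the tests will be unstratified. A van Elteren or stratified log-rank test would fit its wording. This stands in part: the SAP may already settle the matter. But the article is not silent. It names three tests that ignore centre in their usual form, directly after a primary model that includes it, and a SAP author following the text would carry them forward.

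A reader might infer more than the document supports:

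- *That every secondary outcome is analysed without centre.* The list is open, and no test is tied to an endpoint.
- *That p-values are miscalibrated as a matter of fact.* This requires centre to be prognostic, and no ICC is given.
- *That confidence intervals are too wide.* The three tests do not themselves yield intervals, and no interval method is stated, so the text gives no basis for this.
- *That size is already 4.4% at ICC 0.05.* That comes from the approximation for a mean. The named tests, when simulated, were nominal there.
- *That false positives are at risk.* The error runs the other way.

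It is also fair to say that stratifying is not free: the van Elteren test loses power when centre does not matter.

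**Conclusion.** The point holds as a minor inconsistency between the design and primary model on one side and the tests named for secondary outcomes on the other. If centre is prognostic, the cost is mild conservatism and a small loss of power: negligible at an ICC of 0.05, modest at 0.10 and noticeable but still limited at 0.20. These sizes rest on assumed ICCs on a latent scale, assumed centre numbers and block size, and a 0.5 SD shift borrowed from the primary endpoint; they are illustrations, not predictions. The primary analysis already handles centre, so the trial's main conclusion does not depend on this. What is at stake is the precision and coherence of the secondary results.

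**What to change.** In the Statistical analysis section, and in the SAP before database lock, state that secondary analyses account for centre as the primary model does:

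- mortality at fixed time points: mixed-effects logistic regression with random centre, or Cochran-Mantel-Haenszel;
- time-to-event outcomes: centre-stratified log-rank test, or Cox regression accounting for centre;
- support-free days and length of stay: a random-centre model, or van Elteren with small centres pooled.

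Report centre-adjusted effects with 95% confidence intervals, and name the interval method. If unstratified tests are kept for any endpoint, give the reason.

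The cost is wording only, since centre is the stratification factor and is therefore known for every randomised patient. The statistical downside is the possible 1-2 point power loss with van Elteren if centre has no effect. That is a reason to prefer random-centre models, or to pool small centres by a rule fixed in advance.
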